### Controls

The IMT measurements will be compared to the baseline measurements and the elastography measurements will be compared to an age and sex matched control group of patients who had a stroke and at least one of the following cerebrovascular risk factors: hypertension, diabetes, smoking, hypercholesterolemia and atrial fibrillation. The cognitive performances of all patients will be compared to available normative reference values (adjusted for age and education level). Finally, the frequency of silent brain infarctions and white matter lesions will be compared to the frequency in patients without RT of the neck, as described in prior population based studies
[12,13].

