## Background

Successful treatment options for cancer have resulted in more long-term survivors, prone to long-term complications of chemotherapy and radiotherapy (RT). A well-known long-term complication of RT of the neck is carotid artery vasculopathy, which ultimately can lead to stroke
[1,2].

Apart from acute neurological complications, like a cerebral infarction, evidence from daily clinical practice shows more subtle, slowly progressive deficits in cognitive and motor functioning. These long-term cerebral and vascular complications in young survivors of cancer are a serious potential problem that hamper reintegrating in social functioning and work. The longer survival stresses the need for a long-term follow-up study that assesses the long-term complications of RT induced carotid artery vasculopathy. To date, no such studies exist to the best of our knowledge.

We hypothesize that RT of the neck accelerates carotid atherosclerosis with secondary development of cerebral vascular lesions. These vascular cerebral changes are subsequently related to cognitive and motor functioning with a major impact on activities of daily social functioning. A better understanding of the underlying pathophysiology of this RT induced vasculopathy is needed for prognostic purposes and can be used to develop strategies that prevent further progression and thereby reducing the risk of future stroke and neurological impairments.

The current study aims to investigate four questions. The first question focuses on the relation between RT and long-term carotid artery-wall changes. We hypothesize that irradiation induces premature atherosclerosis which is different from more common atherosclerosis due to classic cerebrovascular risk factors. We therefore study the location and composition of post-irradiation vessel-wall changes with advanced imaging techniques; plaque and Intima Media Thickness (IMT) analysis on ultrasound with innovative vessel-wall elastography and magnetic resonance imaging/angiography (MRI)/(MRA)
[3-5]. The second question examines the relation between RT and long-term cerebral vascular changes. In the general population the prevalence of silent brain infarcts (SBI) is up to fivefold higher than that of acute stroke
[6]. SBI are related to impaired cognitive functioning, dementia, stroke and gait and balance disorders
[7]. Carotid artery pathology increases the risk of SBI

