**Radiotherapy**		
Dosis Total (Gy)	X	X
Dosis per fraction (Gy)	X	X
Number of fractions	X	X
Bilateral/unilateral	X	X
Dose on common carotid artery	X	X
Dose on internal carotid artery	X	X

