#### Carotid artery ultrasound - Intima Media Thickness measurement

The measurement of IMT at follow-up 7 years after RT was exactly the same as described at baseline.

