### Outcome events

#### Imaging outcomes

Firstly, on ultrasonography, the IMT of the carotid artery 6 years after RT will be compared with the IMT at baseline. Furthermore, the strain in the vessel wall and plaque 6 years after RT will be measured and compared with a control group. Secondly, on MRI/A of the carotid arteries the degree of stenosis, location and when possible composition of vessel wall changes (lipids, fibrosis, hemorrhage) will be scored, according to an in house developed protocol.

All MRIs of the brain will be scored semi-quantitatively by two neuroradiologists separately for white-matter lesions (WML), brain atrophy and (silent) brain infarctions using validated scales
[34-36] and in case of disagreement a consensus meeting will be held.

Furthermore, total white matter lesion volume will be calculated by a prior published, in-house developed, validated technique
[37]. In short, WML are defined as hyperintensive lesions on FLAIR MRI without corresponding cerebrospinal fluid like hypo-intense lesions on the T1 weighted image. Gliosis surrounding lacunar and territorial infarcts is not considered to be WML. Finally, brain volumetry will be done to measure total white and grey matter volumes. Grey and white matter tissue and cerebrospinal fluid probability maps will be computed by using a six class segmentation tool in Statistical Parametric Mapping Software (http://www.fil.ion.ucl.ac.uk/spm) (SPM 8) on the T1 MPRAGE images. Total grey and white matter volumes are calculated by summing all voxel volumes belonging to the tissue class. Total brain volume is taken as the sum of total grey and total white matter volume. Co-registration parameters of the FLAIR image to the T1 image are computed (SPM8 mutual information co-registration) and used to bring both the FLAIR and WML segmentation images into the subjects (anatomical) reference frame. Transformed images will visually be checked for co-registration errors. Subsequently, the WML segmentations are re-sampled to and combined with the white matter maps to yield to a WML map (the intersection of WML and white matter) and NAWM map (the complement of WML in white matter) in the T1 reference space.

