**Demografics**	
Male (%)	60
Age at baseline, years (mean, SD)	54.3 (13.3)
Follow-up post RT, years (mean, SD)	6.7 (1.2)
Age at FU, years (mean, SD)	61.2 (13.4)

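### Carotid IMT is compared only with the same patients' pre-radiotherapy baseline, so the stated comparison cannot separate a radiotherapy effect from ageing and changing risk factors

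*Protocol article*

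**What the plan says.** The Controls section of the protocol article gives each outcome its own reference. For IMT it is the patients themselves: "The IMT measurements will be compared to the baseline measurements". The Imaging outcomes section repeats this: "the IMT of the carotid artery 6 years after RT will be compared with the IMT at baseline".

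Other outcomes get an outside reference. For strain, "the elastography measurements will be compared to an age and sex matched control group of patients who had a stroke". For cognition, "The cognitive performances of all patients will be compared to available normative reference values (adjusted for age and education level". Silent infarcts and white matter lesions are set against published population studies of people without neck RT.

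The IMT comparison serves the first aim in the Background: "The first question focuses on the relation between RT and long-term carotid artery-wall changes". The hypothesis stated there is that neck RT accelerates carotid atherosclerosis.

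The Statistical analysis section offers t tests, analysis of (co)variance or nonparametric tests for continuous variables, and logistic regression to adjust for confounding. It does not give IMT an unirradiated or dose-based contrast. Table 1 schedules carotid dose ("Dose on common carotid artery", and likewise for the internal carotid) and laterality of RT.

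**The concern.** Acceleration means change beyond the ordinary rate, so testing it needs some estimate of the ordinary rate. The named comparison has none. Every patient is exposed and every patient ages over the same interval, so time and RT are completely confounded in the mean change.

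Risk factors also moved between the two visits, and not all in one direction. An IMT increase could therefore be expected without any RT effect, and a significant paired test would say little about the hypothesis. At stake is the IMT part of the answer to the first research question.

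**Working it through.** The article states no alpha, power, IMT effect size or IMT SD, so there is no design figure to reproduce.

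**Elapsed time (Table 2).** Mean age goes from 54.3 to 61.2 years: 61.2 − 54.3 = 6.9. Mean follow-up after RT is 6.7 years (SD 1.2). I use 6.7.

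**Risk factors (Table 2, n = 65).**

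| Factor | Baseline | Follow-up | Change (points) |
|---|---|---|---|
| Hypertension | 26% | 69% | +43 |
| Hypercholesterolemia | 9% | 39% | +30 |
| Diabetes | 5% | 11% | +6 |
| Obesity | 8% | 12% | +4 |
| Current or recent smoking | 51% | 22% | −29 |

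**Sample for paired IMT.** The Results report 51 patients seen in person and 14 followed by telephone (51 + 14 = 65). Paired IMT can exist for at most 51.

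**Probability of significance when RT has no effect.** Assumptions, not in the article: ageing adds r mm per year; the within-patient change has SD s; two-sided 5% paired t test.

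- Drift = r × 6.7, so 0.005 gives 0.0335 mm, 0.0075 gives 0.050 mm and 0.010 gives 0.067 mm.
- Standardised drift d = drift / s; noncentrality = d × √51, with 50 degrees of freedom.
- Example: r = 0.0075 and s = 0.15 give d = 0.050 / 0.15 = 0.335, noncentrality 0.335 × 7.14 = 2.39, probability 0.65.

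| Ageing rate (mm/year) | SD 0.10 | SD 0.15 | SD 0.20 |
|---|---|---|---|
| 0.005 | 0.65 | 0.35 | 0.22 |
| 0.0075 | 0.94 | 0.65 | 0.42 |
| 0.010 | 0.997 | 0.88 | 0.65 |

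In units of the SD of change, drift of 0.1, 0.2, 0.3 and 0.4 SD gives 11%, 29%, 56% and 80%. With zero drift it is 5%.

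**What a side-to-side contrast could offer.** Table 2 gives 37% unilateral RT: 0.37 × 65 = 24 patients, or 0.37 × 51 = 19 of those seen if the share is the same. Ageing and systemic risk factors act on both sides and largely cancel. A paired t test then has 80% power for a side difference of 0.60 SD (n = 24) or 0.68 SD (n = 19), where the SD is that of the side difference. Converting this to millimetres would need the correlation between sides, which the article does not give.

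**The case against.** The strongest reply is that the article never says the whole change will be called an RT effect. A reader might infer from the comparison that all IMT growth will be attributed to RT, but the text does not support that reading. The Methods state the aims as frequency, pathophysiology and outcome, and a before-after change can legitimately describe what happened to these patients. No primary outcome is named, and the first question also draws on elastography and carotid MRI/MRA. The fourth question relates baseline treatment characteristics to vasculopathy, and analysis of covariance is allowed. All this is fair and limits the point to what the IMT comparison can show. It does not remove it. The comparator is stated twice and is not merely left open. Covariates cannot identify an RT effect when everyone is exposed and no dose or side contrast is in the model, and logistic regression does not suit a continuous change.

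A second tempting reading is that the study already holds an unused internal control in the non-irradiated carotid. That is unverified. The baseline Carotid ultrasound section ties the IMT site to the RT field, and the follow-up section says: "The measurement of IMT at follow-up 7 years after RT was exactly the same as described at baseline". Examination of both sides is stated only for elastography. The contralateral IMT may not exist, and the visits had already taken place.

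A third is to read the rise in hypertension as uniform worsening. Smoking fell, the follow-up definitions are not given, and patients with high cholesterol or on statins were excluded at entry, so part of the recorded rise may be ascertainment or selection. Table 2 also covers 65 patients, not the 51 examined.

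Finally, the 6 and 7 years in the text against the mean of 6.7 in Table 2 are loose rounding. The criterion of more than 5 years is consistent, and nothing here depends on the difference.

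**Conclusion.** The point holds in limited form. The IMT comparison that the article fixes can show total change over a mean of 6.7 years. It cannot by itself show that RT accelerated that change.

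The direction follows from the design alone. The size does not: the range of 0.22 to nearly 1.00 rests wholly on an assumed ageing rate, an assumed SD and 51 complete pairs, which is a ceiling. Within those assumptions every value is at least four times the nominal 5%. The documents support neither a claim that the sponsor will misattribute the change nor a claim that a ready-made contralateral control exists.

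**What to change.** - **Controls and Imaging outcomes:** state that the before-after IMT difference is reported as total change since baseline, not as evidence of an RT effect.
- **Main RT analysis:** in all patients with paired IMT, regress IMT change on artery-level dose (common carotid dose for the common carotid, internal carotid dose for the internal carotid), with actual years since RT, age and baseline risk factors. Allow for several arteries per patient, for example with a patient random effect.
- **Supporting analysis:** first confirm whether IMT of the non-irradiated side was recorded in unilateral-RT patients. If it was, add the within-patient comparison of sides: difference in change where both sides have a baseline, otherwise the follow-up difference. If it was not, omit this analysis and say so.

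**Cost.** The dose analysis needs new analysis wording and no new visits, because dose is a scheduled item in Table 1. Both contrasts are less precise than the before-after test. The side comparison would rest on about 19 to 24 patients and leaves out the 63% treated bilaterally. Dose may be associated with tumour type, so the regression is not free of confounding, and its precision depends on how much dose varies, which the article does not report.

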### Patients

A prospective cohort study of head and neck cancer patients in two centers of the Netherlands (the Netherlands Cancer Institute/Antoni van Leeuwenhoek Hospital (NCI/AvL), Amsterdam and the Radboud University Medical Center Nijmegen) was initiated.

At baseline, patients were eligible for inclusion if they received RT of the neck because of a T1/T2 (N0M0) laryngeal carcinoma, T1/T2 (N0M0) parotid carcinoma/pleomorphic adenoma, T1/2 (N1/2 M0) naso/oro/hypopharynxcarcinoma or non-Hodgkin/Hodgkin lymphoma. Originally, the study was designed as an open-label multicentre Prospective Randomized Open Blinded Endpoint (PROBE) study to assess the effect of an HMG-coA reductase inhibitor (atorvastatine) on carotid IMT in the first 2 years after irradiation of the neck. Because of dwindling accrual the study was redesigned to a prospective cohort study. The initial exclusion criteria were: a history of cerebrovascular disease, pregnancy or breast-feeding, ongoing treatment with an HMG-coA reductase or cytochroom P450 inhibitor, active liver disease or > 3 times the upper limit of serum transaminases, 5 times the normal level of creatine phosphokinase, serum cholesterol > 7 mmol/L and a life expectancy < 2 years. All patients gave written informed consent.

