#### Non-invasive carotid ultrasound elastography – imaging protocol

Following IMT measurements, the distal CCA and proximal ICA at both sides were examined in a longitudinal and transverse imaging plane using a Medison Accuvix V10 ultrasound system (Samsung Medison Seoul, Republic of South Korea) equipped with an L5-13 linear array transducer (fc = 8.5 MHz). Firstly, longitudinal recordings were acquired. After optimum visualization of the cross section with the highest amount of luminal narrowing, an imaging mode called radial zone mode was turned on, which enabled us to perform angle compounding and to store raw ultrasound radiofrequency (RF) data (fs = 61.6 MHz). RF data were acquired at three insonification angles (0°, 20° and -20°) for 3 seconds at a frame rate of at least 129 Hz (43 Hz/angle). Insonification angles were relative to the unsteered ultrasound beam direction and changed sequentially before every new ultrasound image frame. Depending on the heart rate, this resulted in the recording of at least two complete cardiac cycles. After the described measurement, the systolic and diastolic blood pressures in the brachial artery were determined using a sphygmomanometer (Littmann® Classic II S.E.; 3 M, St Paul, MN, USA). The pressure values were used to normalize the distensibility and strain results as explained later, since the level of strain is not only related to tissue composition but also to the pressure differential between the subsequently acquired frames. Above described steps were repeated during imaging in the transverse plane. Location of transverse image acquisition was chosen at the vessel wall displaying the thickest IMT. The distance between this cross-section and the carotid bulb was used as an anatomical reference point. Subsequently, this protocol was repeated for the internal carotid artery. The entire measurement series was completed within 30 minutes. Raw RF data were subsequently analyzed to determine distensibility and strain using in-house written elastography software (MATLAB 2010b, the Mathworks, Natick, MA, USA). Detailed description of this can be found in Additional file
1.

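### Carotid strain is compared only with stroke patients, so the elastography contrast cannot isolate an effect of radiotherapy; a side-to-side and dose contrast from data already collected should be added

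*Protocol article*

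**What the plan says.** - **Comparator.** Under Controls, elastography is set against "an age and sex matched control group of patients who had a stroke and at least one of the following cerebrovascular risk factors". In full, the second condition is "at least one of the following cerebrovascular risk factors: hypertension, diabetes, smoking, hypercholesterolemia and atrial fibrillation". Matching is on age and sex. The Imaging outcomes section likewise sets strain against a control group and states no other strain contrast.
- **Timing.** Table 1 marks elastography at follow-up only. IMT is marked at both visits.
- **Cohort selection.** Under Patients: "The initial exclusion criteria were: a history of cerebrovascular disease".
- **Question and hypothesis.** The Background says: "The first question focuses on the relation between RT and long-term carotid artery-wall changes". It then hypothesises that "irradiation induces premature atherosclerosis which is different from more common atherosclerosis due to classic cerebrovascular risk factors", and names elastography among the techniques used to study this.
- **Data at hand.** In the elastography protocol, "the distal CCA and proximal ICA at both sides were examined in a longitudinal and transverse imaging plane". Table 2 gives 63% bilateral and 37% unilateral RT. Table 1 lists the dose to the common and to the internal carotid artery.

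**The concern.** The two groups differ in RT, and by selection they also differ in stroke: one was chosen because a stroke had occurred, the other was screened at entry to exclude cerebrovascular disease. Strain has no pre-RT value, so unlike IMT it cannot fall back on each patient's own baseline. Everything that elastography says about RT then rests on a comparator that carries vascular disease of its own. The imaging protocol also seeks the site of greatest narrowing and of thickest wall, so wall disease in the controls enters their measurement directly.

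At stake is how the result is read. Similar strain could be reported as no RT effect, or as RT damage on a par with that of a stroke patient. A difference could be credited to RT when it reflects only the controls' disease.

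**Working it through.** The article gives no sample size, effect size, SD or number of controls for elastography, so there is no figure to reproduce. The figures below are illustrations. Assumptions: two-sided 5%, 80% power, effects in SD units, controls without neck RT (the Controls section does not say so), and no scan in the 14 patients followed by telephone.

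**1. What the group contrast estimates.** If RT worsens strain by *r* and the controls' disease worsens it by *c*, the expected difference is *d* = *r* − *c*. With 51 patients and an assumed 51 controls, the standard error in SD units is √(2/51) = 0.198, and

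P(reject) = Φ(|d|/0.198 − 1.96) + Φ(−|d|/0.198 − 1.96).

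| RT effect *r* | Controls' disease *c* | *d* | P(reject) |
|---|---|---|---|
| 0.6 | 0.6 | 0 | 5% |
| 0 | 0.6 | −0.6 | 86% |
| 0.6 | 0.3 | 0.3 | 33% |
| 0.3 | 0.6 | −0.3 | 33% |
| 0.6 | 0 | 0.6 | 86% |

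For |d| = 0.6: 0.6/0.198 = 3.03, and Φ(3.03 − 1.96) = 0.86. In row 1 a real RT effect vanishes. In row 2 a difference appears without one. Since *c* is unknown, the bias has no fixed direction.

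**2. Precision of the group contrast.** Detectable difference = (1.960 + 0.842) × √(1/51 + 1/n₂):
- n₂ = 25: 0.68 SD
- n₂ = 51: 0.56 SD
- n₂ = 102: 0.48 SD

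More controls narrow the interval around *r* − *c*; they do not separate *r* from *c*.

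**3. Size of the within-patient set.** From Table 2 (n = 65), unilateral RT is 0.37 × 65 = 24 patients and bilateral 0.63 × 65 = 41. Of the 65, 51 were seen and 14 had telephone follow-up. The number of unilateral patients among the 51 is not given:
- proportional: 0.37 × 51 = 18.9, about 19
- lowest: 24 − 14 = 10
- highest: 24

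**4. Precision of the paired contrast.** Detectable difference from the noncentral *t* distribution with n − 1 degrees of freedom, in SDs of the paired differences:
- n = 10: 1.00
- n = 19: 0.68
- n = 24: 0.60

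These units are not those of step 2. With equal variances on both sides and correlation ρ between a patient's two arteries, the SD of the differences is SD × √(2(1 − ρ)), and ρ is not given.

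**The case against.** The strongest defence is that the comparator is deliberate. The Background hypothesises that RT vasculopathy differs from atherosclerosis due to classic risk factors, and patients with stroke and such risk factors are a recognisable reference for that. Whether RT changes the wall at all is addressed by IMT against each patient's own baseline. This stands in part: the control group is not a plain error. But the first question is also put as the relation between RT and wall changes, elastography is listed among its tools, and nothing in the article limits what the stroke comparison may be used to conclude. Even for the narrower hypothesis, a difference may reflect less disease in a cohort screened for cerebrovascular disease.

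A second defence is that the Statistical analysis section provides for analysis of covariance and adjustment for confounders. That can deal with measured risk factors. It cannot separate RT from stroke when the groups were selected on both.

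Several stronger readings are tempting, and the documents do not support them:
- **Stroke in 100% of controls against 0% of the cohort.** The exclusion applied at entry. Strain was measured more than 5 years later, cerebrovascular events are a study outcome, and the stroke status of the scanned patients is not given.
- **A risk-factor imbalance of 100% against 91% or 68%.** From Table 2, 100 − 9 = 91% had at least one risk factor at follow-up and 100 − 32 = 68% at baseline. Both refer to all 65 patients. The first uses a wider list than the controls' (it adds overweight, migraine and family history). The second precedes elastography by years.
- **Bias towards no difference.** This holds only if RT acts in the same direction as the controls' disease; row 2 of the table shows the opposite case.
- **An internal control in every patient because both sides are scanned.** Only the 37% with unilateral RT have one, and their other artery may have received some dose.

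**Conclusion.** The point holds in a limited form. As the sole strain comparator, with no pre-RT elastography, the stroke group cannot show whether RT changes wall strain. It may still inform the comparison of RT with common atherosclerosis. Irradiated arteries that came out worse than the controls' would be suggestive of an RT effect, but only if the controls' disease does not improve strain and the groups are otherwise alike. Equal or better strain would be uninformative about RT.

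The size of the bias cannot be computed, because the controls' disease effect is unknown; the 5% and 86% rest on assumed effects of 0.6 SD and an assumed 51 controls. A reader might infer that the within-patient contrast should become the primary one, or that controls qualifying through atrial fibrillation alone should be dropped. Both are debatable. The article names no primary strain contrast, and the paired set leaves out the larger, bilateral part of the cohort. The case is for a cheap addition to the analysis.

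**What to change.** In the Controls and Imaging outcomes sections:

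1. Add a paired comparison of strain and distensibility between the irradiated and the contralateral carotid in patients with unilateral RT. Report the number of pairs.
2. Add an analysis of strain by artery-level dose in all scanned patients, allowing for the correlation of arteries within a patient. This also handles any dose to the contralateral side.
3. Limit conclusions from the stroke-control comparison to RT versus common atherosclerosis, with adjustment for the measured risk factors.

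The cost is analysis work and wording: the recordings on both sides exist and carotid dose is on the assessment schedule. Table 1 does not say whether left and right doses are held separately; if they are not, they would have to be retrieved. The downside is low precision: with 10 to 24 pairs, a moderate side-to-side difference could be missed, so a null paired result should be reported with its interval and not read as absence of an effect.

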**MRI**		
Brain (T1, T2, FLAIR)		X
Carotid arteries (TOF, PCA, T1, T2, PD)		X

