### Statistical analysis

Analysis of continuous variables will be done with Student’s *t* test or analysis of (co)variance or in case of skewed distributions which cannot be normalized by log transformation corresponding nonparametric tests will be used. Chi-squared test will be used for analysis of categorical variables and logistic regression analyses will be used to adjust for potential confounding factors.

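### No age, sex or risk-factor standardisation is stated for the comparison of silent infarcts and white-matter lesions with published population figures, so the difference may be biased in either direction

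*Protocol article*

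**What the plan says.** The Background sets the aim: "The second question examines the relation between RT and long-term cerebral vascular changes". For silent infarcts and white-matter lesions, the Controls section names one comparator: "white matter lesions will be compared to the frequency in patients without RT of the neck, as described in prior population based studies". Nothing is said there about age, sex or vascular risk factors.

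The same section controls the other two external comparators. For elastography, "the elastography measurements will be compared to an age and sex matched control group of patients who had a stroke". For cognition, the reference is "available normative reference values (adjusted for age and education level".

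The Statistical analysis section adds one general sentence: "logistic regression analyses will be used to adjust for potential confounding factors". It is not tied to any particular comparison.

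In Table 1, brain MRI is marked at follow-up only. Under Imaging outcomes the infarcts are scored on scales, and "total white matter lesion volume will be calculated" from the same scans.

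**The concern.** A frequency in an examined cohort is set against a frequency observed in other people, and the difference is to inform on RT. Silent infarcts and white-matter lesions depend on age and vascular risk, so a difference in age mix or risk profile enters that difference in full.

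The cohort is not a population sample, and its selection works both ways. At follow-up 69% had hypertension and 22% smoked or had stopped within 3 years (Table 2). At entry, on the other hand, "The initial exclusion criteria were: a history of cerebrovascular disease", together with statin use and cholesterol above 7 mmol/L. The net direction cannot be read from the document.

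Intima media thickness has a baseline measurement; brain lesions do not. No within-patient change can therefore stand in for the external comparison, and lesions that pre-date RT cannot be separated from later ones. At stake is the answer to the second study question.

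**Working it through.** **Inputs from the article.** 51 patients were seen for the follow-up protocol, which includes MRI, and a further 14 by telephone (Results). Age at follow-up is 61.2 years (SD 13.4), hypertension 69% and unilateral RT 37% (Table 2). Table 2 is for n = 65 = 51 + 14, so applying its figures to the 51 scanned patients is an approximation.

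**No figure to reproduce.** The article gives no reference prevalence, reference age, target difference or power for this comparison.

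**Step 1: can the planned regression repair it?** Logistic regression needs covariates for each person on both sides of the contrast. A published frequency supplies none. Adjustment would need individual reference data or stratum-specific rates, and neither is mentioned.

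**Step 2: how large could age bias be?** All of the following are assumptions:
- Model: logit(prevalence) = b0 + ln(OR per decade) x (age - 61.2)/10 + ln(OR for RT).
- OR per decade of age: 1.5, 2.0 or 2.5.
- b0 is set so that an unirradiated population with the cohort's ages has a prevalence of 8%, 12% or 20%.
- Ages are normal, limited to 18-95.

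The table shows cohort minus reference in percentage points, as the range over the nine combinations.

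| Reference mean age (SD) | No RT effect | RT OR 1.5 | RT OR 2 |
|---|---|---|---|
| 50 (10) | +3.0 to +12.0 | +6.4 to +17.8 | +9.5 to +22.4 |
| 55 (10) | +1.9 to +8.4 | +5.4 to +14.1 | +8.5 to +18.8 |
| 61.2 (13.4), as cohort | about 0 | +3.0 to +6.8 | +5.7 to +12.5 |
| 65 (8) | -0.1 to -2.0 | +2.8 to +5.2 | +5.6 to +10.9 |
| 70 (8) | -2.3 to -9.8 | -4.3 to +1.6 | +0.5 to +7.3 |
| 75 (6) | -4.2 to -18.7 | -12.9 to -0.7 | -8.4 to +3.5 |

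The third row is what standardisation to the cohort's ages would recover: no bias under no effect, and a positive difference for an OR above 1.

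**Step 3: hypertension alone.** Difference = (0.69 - h) x (p1 - p0), where h is the reference share with hypertension, p0 the prevalence without it and p1 the prevalence with it. Take p0 = 12% and an OR of 2.5:
- The odds are 0.12/0.88 x 2.5 = 0.341, so p1 = 25.4%.
- At h = 30%: 0.39 x 13.4 = +5.2 points.
- At h = 80%: -0.11 x 13.4 = -1.5 points.

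These are the extremes over p0 of 8% or 12%, OR 1.5 to 2.5 and h from 30% to 80%.

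**Step 4: precision at n = 51.** An illustrative count of 6/51 = 11.8% has an exact 95% interval of 4.4% to 23.9%. Against a reference sample 20 times larger, power for a true OR of 2 is 43%, 51% and 61% at reference prevalences of 8%, 12% and 20%.

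**Step 5: what the unilateral patients can carry.** 0.37 x 51 = 18.9, so about 19 patients if the share holds among those scanned. With all discordant pairs in one direction, the exact two-sided McNemar p-value is 2 x 0.5^k. For k = 5 this is 0.0625 and for k = 6 it is 0.031, so at least 6 one-sided discordant pairs are needed. At an infarct prevalence of 10-20%, 19 patients yield about 2 to 4 with any infarct.

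**The case against.** The strongest reply is that this is a condensed article. It names the comparator and stops; it does not say that the comparison will be unadjusted, and the full protocol or analysis plan may apply age-specific rates. That stands to this extent: one may say that no standardisation is stated, not that the plan has decided against it. It does not dispose of the point, because the same paragraph takes care to state age control for the other two comparators, and the one general adjustment sentence cannot work on aggregate figures.

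A reader might infer that the sign of the RT effect turns on who was in the reference populations. The documents do not support that. They give no reference ages, and the table rests on assumed ones. If those populations are close in age to the cohort the age bias is small; with a true OR of 1.5 the sign holds up to a reference mean age of 65, and with an OR of 2 up to 70.

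A reader might also take the cohort as half smokers from the 51% in Table 2. That is the baseline figure; at follow-up, when MRI is done, it is 22%. The hypertension threshold given at baseline is broad (above 130/80 mmHg or medication), so the 69% may not be comparable with other studies' definitions.

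Finally, part of the internal analysis is in reach of the existing plan: carotid doses are collected, and the Background announces an analysis of treatment characteristics against vasculopathy. That makes the addition cheap. The missing pre-RT MRI is a fixed design limit that standardisation does not remove.

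**Conclusion.** The point holds in a limited form. The only comparator named for silent infarct and WML frequency is external and aggregate, with no age, sex or risk-factor standardisation stated, no usable adjustment elsewhere in the article and no brain MRI before RT. The difference may be biased in either direction.

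Under the assumed prevalences and gradients, a reference about a decade older than the cohort shifts the difference by 2.3 to 9.8 points with no RT effect. An RT OR of 2 is worth 5.7 to 12.5 points once ages agree. The bias can thus be of the same order as the effect, in a sample with at most moderate power. The actual size and sign remain unknown because the reference ages are not given.

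**What to change.** 1. **Standardise the external comparison.** Apply the reference studies' age- and sex-specific rates, where published, to the examined patients: E = sum of r(age_i, sex_i). Report observed/E with an exact interval, for lesions defined as in the reference study. Call the result descriptive. Where stratum rates are not published, say so and show the figures side by side without an RT claim.
2. **Add internal contrasts.** In unilaterally irradiated patients, compare ipsilateral with contralateral WML volume as a paired analysis; the WML maps are already placed in each subject's own T1 space. Across all patients, regress WML volume on carotid dose, adjusted for age, sex, smoking and hypertension.
3. **Report lateralised infarcts descriptively only.** A McNemar test on about 19 patients cannot carry a claim.
4. **State the limits.** There is no brain MRI before RT, and the age and risk-factor figures should be given for the 51 scanned patients rather than the 65 in Table 2.

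The cost is slightly more analysis work and no new visits or scans. It depends on what the reference publications tabulate, and precision will be low, which the report should say.
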